## Abstract

Introduction: Silver Diammine Fluoride (SDF) is an emerging caries preventive treatment option that is inexpensive, safe, and easily accessible. The evidence is clear that the use of SDF at concentrations of 38% is effective for arresting caries in primary teeth. However, the determination of an optimal SDF application frequency for a cavitated lesion in pragmatic settings is warranted especially among high dental caries risk groups. Hence, the primary objective of this clinical trial is to compare the effectiveness of annual, bi-annual, and four times a year application of 38% SDF application in arresting active coronal dentinal carious lesions on primary teeth among tribal preschool children aged 2–6 years. Methods and Analysis: This study is designed as a randomized, controlled trial consisting of three parallel arms with an allocation ratio of 1:1:1. The trial will enroll 480 preschool tribal children with a cavitated carious lesion (2–6 years) attending a primary health care Centre in Wayanad district, India. Each arm will receive 38% SDF application on an annual (baseline), bi-annual (baseline and 6 months), and four times a year (baseline, 2nd, 4th, and 8th week), respectively. The analysis will be performed both at the tooth- and person-level. Ethics and Dissemination: This trial will be conducted following the principles of the Declaration of Helsinki and local guidelines (Indian Council of Medical Research). The protocol has been approved by Institutional Review Committee (IRB). This trial has been registered prospectively with the Clinical Trial Registry of India [Registration No: CTRI/2020/03/024265].

## 1. Introduction

Dental caries is the most common chronic childhood disease, posing a significant public health problem [1]. Oral diseases have considerable social and economic impacts on the individual and community [2]. Early Childhood Caries (ECC) is a major public health problem worldwide. ECC prevalence varies, but the underprivileged children, across cultures, have a greater proportion of vulnerability [3]. The prevalence of ECC in Indian preschool children ranges from 12% to 94.3% [4,5,6,7]. Untreated ECC can cause pain and can lead to multiple consequences such as difficulty in eating, speaking, and attending to learning as it occurs during the years of milestone development of the child [8]. 

ECC are relatively inexpensive to prevent [9,10,11,12,13], yet becomes extremely burdensome on the children and families, and expensive to treat once lesions cavitate in young children who need extensive treatment or are uncooperative and/or have immature cognitive functioning, disabilities, or medical conditions, where treatment under general anesthesia, in most cases in hospital operating rooms, is the standard of care. Effective ECC preventive measures include the use of fluoride varnishes such as 5% Sodium Fluoride (NaF) and the use of fluoridated toothpaste [14]. These agents are beneficial before the onset of ECC. However, if caries has progressed to cavitation due to failure of preventive strategies, then there is a need to arrest the progression of the condition. In the management of cavitated ECC, removal of infected tooth tissue and restoration is recommended which is resource intensive as discussed earlier.

The 38% SDF, approved as a desensitizing agent, has been used (off-label) as a caries-arresting agent. SDF is a water-like liquid that is applied to teeth with active carious lesions. It has a dual effect against caries owing to the presence of fluoride which promotes remineralization and silver which provides antimicrobial action. Furthermore, when bacteria killed by the silver ions are added to the living bacteria, the silver is reactivated thereby effectively killing the live bacteria eliciting a zombie effect [15]. A highly re-mineralized layer with high calcium and phosphate content was observed on arrested dentine caries lesions. Thus, SDF as a chemotherapeutic agent can be used in cavitated lesions of ECC to stop the progression of dental caries.

There have been multiple clinical trials and several systematic reviews reporting the application of SDF causing the arrest of caries lesions in a high percentage of cases (30–70%) [16,17,18,19,20,21,22,23,24]. Nearly 70% of caries lesions in primary teeth would be expected to be arrested in two years after SDF application with the variation of annual or biannual application as compared to combined controls of 5% NaF varnish or restorations. According to the AAPD manual [25], nearly 68% (95% CI = 9.7 to 97.7) of cavitated caries lesions in primary teeth would be expected to be arrested in two years after SDF application with a variety of annual or biannual application as compared combined controls of 5% Sodium fluoride (NAF) varnish or restorations. The American Dental Association (ADA) guidelines recommend the use of 38% SDF twice a year application over 5% NaF varnish (once per week for 3 weeks application) to arrest the cavitated caries coronal lesions in primary and permanent teeth [16]. However, it is a conditional recommendation that implies that not all patients would benefit from the intervention and depends on individual risk for caries, preferences, values, etc.

Studies are comparing various frequencies (thrice a year, weekly, biannual, annual, five times weekly per year, etc.) of SDF; however, the evidence is inconsistent. A clinical trial has shown that the yearly application of SDF has a higher proportion of arrested caries compared to the weekly application [26]. Biannual application of SDF was found to be superior compared to annual application in arresting cavitated carious lesion [27,28,29,30,31]. Annual application of silver diamine fluoride prevented many more carious lesions than application of fluoride varnish four times per year [26,31].

Tribal children face many health disparities compared with the mainland counterparts [32]. The prevalence of ECC is 74.7% in these tribal children compared to their counterparts [7]. The oral health disparities for these children exemplify, many of the inequities and early care services in these communities. SDF as a chemotherapeutic agent for prevention and managing of ECC would be a crunch point as it is a simple technique, acceptable, and cost-effective strategy over restorations and hospital-based management. The SDF effectiveness in these high-risk caries children will generate the evidence to use SDF as a caries preventive tool to the population having less access to regular dental care. The trial findings may also help in reducing pain, improving quality of life, and significantly reducing costs, all contributing to substantial reductions in disparities in caries the disparities in between access to preventive care. The use of SDF to prevent or delay surgical intervention until after the age of 3 years makes it a potentially attractive adjunctive therapy for managing caries in the young pediatric population.

Though the evidence is clear that the use of 38% SDF is effective for arresting dental caries, the determination of an optimal SDF application frequency for a cavitated lesion in pragmatic settings is important especially among high caries risk tribal children who have poor access to oral care. Thus, the primary objective of this trial is to compare the effectiveness of an annual, semi-annual, and four times a year application of 38% Silver Diammine Fluoride in arresting active coronal carious lesions on primary teeth of tribal preschool children in India. The secondary objective is to assess the acceptability of SDF treatment by the child as well as parent/s.

## 2. Methods

### 2.1. Study Design

This trial is designed as a randomized, controlled trial consisting of three parallel arms with an allocation ratio of 1:1:1 (Figure 1).

### 2.2. Study Settings

The trial will be conducted in a primary health care center at Kalpetta, Kerala, India. Kalpetta is the headquarters of Wayanad district which has the largest tribal population in the state of Kerala.

### 2.3. Trial Registration

The trial protocol has been registered with the Clinical Trial Registry of India at http://ctri.nic.in accessed on 10 May 2021. (Registration No CTRI/2020/03/024265 dated Registered on 25 March 2020). Recruitment of study subjects will begin in April 2021 and the trial is expected to conclude by December 2023. This clinical trial protocol has been developed following the SPIRIT 2013 Statement (https://www.spirit-statement.org/ accessed on 10 May 2021).

### 2.4. Study Population

Tribal preschool children aged two to six years attending the primary health care center for routine dental/medical care and with one or more cavitated dentinal carious lesion present in any surface of the primary teeth will constitute the sampling frame for the study.

### 2.5. Eligibility Criteria

#### 2.5.1. Inclusion Criteria

Children of any gender aged 2–6 years with the presence of cavitated caries lesion classified as stage 5–6 following the Modified International Caries Detection and Assessment System (ICDAS).The parent of the child understands the importance of SDF treatment to arrest prevent dental caries.Parent of a child willing to accompany the child at required intervals for evaluation.

#### 2.5.2. Exclusion Criteria

Children with ulcerative gingivitis or stomatitis.Developmental dental abnormalities such as enamel defects.Serious chronic medical conditions, such as congenital heart disease.Cavitated teeth that are nearing natural exfoliation time.Children with more than one-third of the crown missing, or pulpal involved (tooth with pulp exposure, presence of an abscess or a sinus, obvious discoloration, and premature hypermobility were regarded as pulpal involved tooth)Known silver allergy.Uncooperative children (after the failure of basic pediatric patient management protocols)Children with special health care needs.

### 2.6. Definition of Study Condition (Dental Caries)

A cavitated lesion is a carious lesion with a surface that is not macroscopically intact and with a distinct discontinuity or breaks in the surface integrity [33]. The tooth should be classified as stage 5 or 6 according to Modified International Caries Detection and Assessment System (ICDAS) [25].

The status of the dentinal caries lesions will be assessed by visual inspection aided by tactile detection using a Community Periodontal Index (CPI) probe. An artificial light source from the dental chair will be used. The tooth surface will be dried and a CPI probe with the tip gently passed over the entire surface of the cavity to detect and confirm the visual evidence of caries. Cavities with yellowish/brown rough wall/floor which could be easily penetrated by the probe will be diagnosed as active. Five surfaces in each posterior tooth (occlusal, buccal, lingual, mesial, and distal) and four surfaces in each anterior tooth (labial, lingual, mesial, and distal) will be assessed. Radiographic aids will not be used for the diagnosis of caries.

### 2.7. Interventions

#### Silver Diammine Fluoride

SDF is a colorless liquid containing silver ionic particles. It contains 38% (44,800 ppm) fluoride ion at a pH of 10. This formulation constitutes 25% silver, 8% ammonia, 5% fluoride, and 62% water. One drop (0.05 mL) of 38% SDF solution (2.24 F-ion mg/dose) is required for the treatment of one tooth. The SDF treatment protocol consists of removing gross debris from the cavitated tooth, drying the affected area, isolating the tooth with the help of cotton rolls and suction, placing a small amount of SDF on the affected area, gently drying the SDF for 1 min, removing excess SDF with cotton gauze and isolating the tooth for up to 3 min [34]. This procedure will be performed after the tooth is removed of debris (with the aid of a toothbrush) and soft caries using a spoon excavator. It includes gross debris from cavitation to allow better SDF contact with denatured dentin. Carious dentin excavation before SDF application is not necessary. As excavation may reduce the proportion of arrested caries lesions that become black, it may be considered for esthetic purposes. No rotary instruments will be used for caries removal.

The study participants will be allocated into one of the three parallel arms who will receive 38% SDF application as follows:
Study arm 1: annually (once a year; baseline visit);Study arm 2: bi-annually (twice a year at 6-month intervals; baseline visit and after 6 months);Study arm 3: four times a year (baseline visit, 2nd, 4th, and 8th week).

In the baseline visit in all the study arms, the child will be assessed for cavitated caries lesions and caries risk (ADA Caries Risk Assessment Form (Age 0–6)). After obtaining consent for the trial, SDF is applied on the selected caries teeth depending on the study arm. The demographic characteristics, plaque index, and caries status will be assessed. In the subsequent visits depending on the study arm, SDF will be applied (Table 1).

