### 2.8. Primary Outcomes

The primary outcome of the study is the arrest of caries. The hardness of treated cavitated surfaces of teeth on probing (periodontal probe) is an indication that a lesion is arrested. Blackish discoloration of surface/cavity alone will not be a criterion for defining the arrested caries.

The outcome assessment will be performed for all the arms at 6 months and 12 months. SDF treated cavities of teeth with arrested caries are defined as surfaces with active cavitated caries at baseline that changed into surfaces with arrested cavitated caries on subsequent assessments. The possible scenarios and their assessment are as follows:Any teeth with treated carious lesions that are lost due to exfoliation will be considered arrested throughout the lifetime of the tooth. For any reason, if the child’s teeth are restored before the trial period, censoring of the data depends on the duration of the trial period the child has participated.The following dental complications due to the evolution of caries will not be considered as caries arrested.○The teeth extracted due to caries progression.○If the SDF treated cavities, caries progressed beyond the dentine.○If the tooth is extracted due to fracture, trauma will not be counted for the study.

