### 2.10. Participation Timeline

Each eligible child will be a part of the trial for one year from their baseline visit. The total number of visits depends on the study arms to which child is allocated (Figure 1).

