## 4. Statistical Methods

The outcome of the treated carious lesion is binary, either arrested lesion or failed to arrest at 6 months follow-up and at the end of 12 months follow up visit. The outcome will be assessed at two levels: Tooth-level—the proportion of cavitated surfaces at baseline will be compared with the proportion of the surfaces arrested at each frequency of application at 6 months follow-up and the end 12 months using chi-square methods. Between three frequencies of application (annual, semi-annual, and four times a year applications) the proportion of arrested surface at 6 months follow-up and end 12 months will be compared. This comparison will be stratified by type of tooth (posterior vs. anterior) and type of surfaces (facials vs. lingual). Child-level—each child may have one or more cavitated carious surface treated with SDF. So, the per-child proportion of cavitated carious lesions at baseline treated with 38% SDF applied at different frequencies that stayed arrested throughout observation will be determined.

The regression will be modelled on the dependent variable as a percentage of the arrested carious lesion per child with another. The two sets of analysis will be done, first, the intention-to-treat set, considering all patients as randomized regardless of whether they received the randomized treatment, and second, the “per protocol” analysis set. The hypothesis that four times application of 38% of SDF superior to other frequencies (annual or semi-annual application) is accepted, only if shown to be superior using both the “intention to treat” and “per protocol” analysis sets.

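### Arm 3 is labelled as a yearly frequency but is a four-application course finished by week 8, so a superiority finding should be limited to that course

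*Protocol article*

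**What the plan says.** Section 2.7 of the protocol article sets out the three regimens:

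- "Study arm 1: annually (once a year; baseline visit")
- "Study arm 2: bi-annually (twice a year at 6-month intervals; baseline visit and after 6 months")
- "Study arm 3: four times a year (baseline visit, 2nd, 4th, and 8th week")

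The abstract repeats the third schedule: "four times a year (baseline, 2nd, 4th, and 8th week), respectively". Table 1 agrees: Group 3 is treated at baseline and at 2, 4 and 8 weeks, and is marked as not treated at 6 and 12 months. So there is no doubt about what arm 3 receives.

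On follow-up, section 2.10 states: "Each eligible child will be a part of the trial for one year from their baseline visit". On measurement, section 2.8 states: "The outcome assessment will be performed for all the arms at 6 months and 12 months".

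The statements that fix the claim use the label alone. The objective at the end of section 1 is to "compare the effectiveness of an annual, semi-annual, and four times a year application of 38% Silver Diammine Fluoride". Section 4 says "The hypothesis that four times application of 38% of SDF superior to other frequencies (annual or semi-annual application) is accepted", on condition that superiority is shown in both the intention-to-treat and the per-protocol sets. Neither statement mentions the 8-week schedule.

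**The concern.** The objective and the acceptance rule read as though the arms were three points on one scale, at one, two and four applications a year. Arm 2 spreads its applications over the year. Arm 3 gives all of them at the start. Nothing in the article explains why a course completed in 8 weeks is presented as a yearly frequency.

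What is at stake is attribution. If arm 3 does better, an intensive initial course explains the result as well as a higher yearly frequency would. If arm 3 does no better than arm 2 at 12 months, its longer gap since the last application explains that as well as the number of applications would. Section 7 plans to pass results and recommendations to local health authorities and community leaders. A reader told that four times a year won, or lost, could picture applications spread through the year. No child in the trial receives that.

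**Working it through.** **Inputs.** Application times are from section 2.7 and Table 1, assessment times from section 2.8, and length of follow-up from section 2.10. I take 6 months as 26 weeks and 12 months as 52 weeks. The plan gives no figure of its own for time since last application, so there is none to reproduce.

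**Formula.** Weeks since last application = week of assessment − week of last application before it.

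| | Applications by 6 months | Weeks since last, at 6 months | Applications by 12 months | Weeks since last, at 12 months |
|---|---|---|---|---|
| Arm 1 | 1 | 26 − 0 = 26 | 1 | 52 − 0 = 52 |
| Arm 2 | 1* | 26 − 0 = 26* | 2 | 52 − 26 = 26 |
| Arm 3 | 4 | 26 − 8 = 18 | 4 | 52 − 8 = 44 |

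*This assumes that the 6-month outcome is read before that visit's application. The article does not state the order. The 12-month column does not depend on it.

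**Concentration of arm 3.** The intervals between its applications are 2, 2 and 4 weeks. All four fall in the first 8 of 52 weeks (8/52 = 15%), and none in the remaining 44 (44/52 = 85%).

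**Do the arms lie on one frequency scale?** If n applications start at baseline and are spread evenly over 52 weeks, the last falls 52/n weeks before the end.

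- Arm 1: 52/1 = 52, which matches its schedule.
- Arm 2: 52/2 = 26, which matches its schedule.
- Arm 3: 52/4 = 13, against an actual 44.

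This is only a yardstick for what the label suggests; it is not a proposed schedule. It shows that arms 1 and 2 fit one scale and arm 3 does not. As the count rises from 1 to 2 to 4, the gap at 12 months goes 52, 26, 44, so it falls and then rises.

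**Arm 3 against arm 2 at 12 months.** The count is 4 against 2. The longest interval between applications is 4 weeks against 26. The time since the last application is 44 weeks against 26. Three features differ at once, and no arm in the trial separates them.

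**The case against.** The case on the other side is substantial, and much of it stands.

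- **The comparison is valid.** The regimens are randomised 1:1:1 and described identically in the abstract, section 2.7 and Table 1. A reader might infer that the trial cannot support its conclusion at all. The documents do not show that: the hypothesis can be tested for the regimens as defined.
- **The label is true as a count.** A child in arm 3 does receive four applications within the one year of participation, and the weeks follow in brackets in the abstract and section 2.7. A reader might infer that label and schedule contradict each other outright. They do not. The label suggests a spread that the schedule does not have, and the objective and acceptance rule carry no bracket to correct the impression.
- **Arm 1 is sound.** One application is what once a year means in a one-year trial, and section 2.7 says so. It limits inference only about annual treatment repeated over several years.
- **The article uses frequency loosely.** Section 1 lists weekly courses beside annual and biannual ones, and section 2.11 draws on a comparison of weekly with annual treatment. This makes a concentrated course a natural arm to study. It also shows that the authors distinguish regimens by timing as well as by count, which is a reason to name the timing in the objective.
- **Arms 1 and 2 also differ in both number and recency.** True, but there both differences go the way a yearly frequency implies. In arm 3 against arm 2 they do not.
- **Optimal frequency is a stated need, not a planned conclusion.** In the abstract and section 1 it is given as background. That is fair, and the point here rests on the objective and the acceptance rule instead.

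Reporting time since last application beside each arm's result would not help: the schedule makes it nearly constant within an arm, so it separates nothing.

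**Conclusion.** The concern holds as a limit on interpretation. Arm 3 is an 8-week course followed by 44 weeks without application. The objective and the acceptance rule describe it as a level of yearly frequency, and a difference between it and the other arms cannot be attributed to that. The difficulty is greatest against arm 2 at 12 months, where arm 3 has twice the applications but a gap since the last one that is 44 − 26 = 18 weeks longer.

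The week counts rest on the 26- and 52-week conversion. The three-day rescheduling allowance in section 2.13 does not alter them materially. No assumption is made about whether number, spacing or recency drives arrest of caries; the point is that the design does not separate them.

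This is more than an editorial matter, because the objective and the acceptance rule fix what the trial will be said to have shown. It is less than a design failure: randomisation, schedules and outcome readings all support a comparison of the three regimens.

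**What to change.** The sponsor should reconcile arm 3's label with its schedule in the abstract, the objective in section 1, section 2.7 and section 4. Which schedule is intended is for the sponsor to settle, and none is proposed here.

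If the schedule in section 2.7 and Table 1 stands:

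1. Restate the objective and the acceptance rule as a comparison of three named regimens: a single baseline application, two applications 6 months apart, and a four-application course over 8 weeks.
2. State that a superiority conclusion for arm 3 concerns that course, and is not a finding about four-times-a-year application or about the optimal frequency.
3. Use the same names in the recommendations planned under section 7.

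The cost is a change of wording, with no change to visits, sample size or analysis. The downside is a narrower claim.
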